^b^Only concomitant medication affecting the haemostasis are registered

## Statistical analysis

All efficacy analyses will be done according to the intention-to-treat principle comprising all patients who receive intervention (active or placebo), even if not completed. This includes all randomized patients fulfilling inclusion criteria and not meeting exclusion criteria. The per protocol population will be a subset of the intention-to-treat population. It includes patients who have received the intervention (active or placebo), but excluding the following patients: patients receiving blood products between time of inclusion and intervention or patients receiving haemostatics such as fibrinogen concentrate, prothrombin complex concentrate or recombinant factor VIIa after the administration of intervention (active or placebo).

Statistical analyses will be performed by a statistician blinded to the allocated treatment prior to the breaking of the randomization code. All outcomes will be reported according to analyses described above. Descriptive statistics will be calculated for all end points. All summary statistics of continuous variables will include: n, mean with standard deviation, or median with interquartile ranges. All summary statistics of frequency tables will include n, % and N, where N is the total number of patients recorded values in the corresponding group.

The change in TEG® FF MA from baseline to the 15-min measurement will be analysed with ANCOVA. The analysis will be adjusted for baseline TEG® FF MA to increase statistical power. The assumption of normality of the residuals will be assessed using QQ-plots and, if a satisfactory fit is not obtained, we will first attempt to conduct the analysis using log-transforms. If the fit is still not adequate, we will employ the Mann-Whitney test to the change values. The primary null hypothesis is that there is no difference between the fibrinogen concentrate arm and the placebo arm.

The secondary end points (number 1–4; Table 2) will be analysed using mixed models, adjusting for baseline values. The models will include an interaction term between treatment group and time. If an overall significant treatment effect is found post hoc pair-wise comparisons will be employed. The assumption of normality of the residuals will be assessed using QQ-plots and, if a satisfactory fit is not obtained, we will first attempt to conduct the analysis using log-transforms. If the fit is still not adequate, we will employ the Mann-Whitney test to the measured changes from baseline to each of the measurement times; i.e. there will be as many Mann-Whitney tests as there are measurement times.

The secondary outcomes (number 5–7; Table 2) will be analysed using Cox models as these are time-to-event outcomes with potential competing risks. The assumption of proportional hazards will be assessed using Schoenfeld residuals. Secondary outcomes (number 7, 9, 10; Table 2) are all categorical and will be analysed using Fisher’s exact test and effects quantified using frequency tables and risk ratios.

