### Randomization

The randomization is done in blocks of six, and the randomization sequence and envelopes are generated and validated by two persons that are otherwise not involved in the trial. Randomization was performed using Microsoft Excel software (Microsoft Corp., Redmond, WA, USA). Treatments (fibrinogen concentrate - Riastap® or placebo/saline) were arranged in two groups of 20 patients in a single column in a systematic order. Each block of six patients included three fibrinogen concentrate - Riastap® and three placebo/saline patients. A second column was created for random numbers and the treatments column was then sorted by these random numbers [21].

Two identical sets of envelopes are generated - one set for randomization of patients at the Trauma Centre, and an “emergency” set for code breaking if necessary. Written and signed documentation for the double-controlled generation of randomization envelopes is kept at the Blood Bank. The randomization sequence is kept secret for the investigators by use of successively numbered, sealed, and opaque envelopes. Each patient is given a unique randomization number.

Emergency department nurses in the Trauma Centre, not involved in treatment of the specific patient, will perform 24-hour on-site randomization by envelope-opening to allow for immediate allocation to either receiving fibrinogen concentrate (intervention) or saline (placebo). A written instruction for the randomization procedure is kept with the envelopes.

A randomization list is held by the sponsor, which will be available to the investigator after the completion of the trial. Emergency code-breaking envelopes are available in the Blood Bank where they can be opened if decided by the sponsor.

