### Interventions

The treating physician must have evaluated the patient’s eligibility and approved the patient’s enrolment in the trial prior to administration of the trial drug/placebo. All patients will be treated according to normal standard of care for haemorrhaging trauma patients.

The trial/placebo drug is administered as an intravenous bolus dose as early as possible during the initial resuscitation (Fig. 1). During the infusion the patient will be observed especially with regard to potential signs of thrombotic and allergic complications.

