### Missing data

If for any of the analyses mentioned above there are less than 95 % of the observations which are complete, we will employ multiple imputation techniques for that analysis [24]. The multiple imputation approach will be based on chained equations. If more than 95 % of the observations are complete, we will only employ complete case analysis.

The power calculation is based on local data finding of a TEG® FF MA mean 13.6 mm (SD ± 5.6) on arrival in trauma patients not surviving for 30 days. Administering 60–70 mg/kg fibrinogen concentrate will result in an approximate increase of 6–8 mm in TEG FF MA according to Tanaka and colleagues, which corresponds to increasing the fibrinogen level with approximately 1 g/l and to a level of above 2.3 g/l [25]. To detect the above difference with a power of 0.90 (1-β) and alpha of 0.05 requires n = 19 patients in each group. We have chosen to include 40 patients, 20 evaluable patients in each randomization group in case of attrition, in the present trial. Patients who drop out or are withdrawn for any reason before hour 24 will be replaced.

No interim analysis is planned. The actual statistical power will be a bit higher as the primary end point is a change value and we adjust the analysis for baseline values. However, the exact size of this additional power cannot be readily assessed as we do not have reliable information about the intra-person correlation of TEG® FF MA.

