### Patient withdrawal

Participation in the trial is strictly voluntary. Patients, relatives or scientific guardians are free to discontinue the trial at any time without giving their reason(s).

A patient must be withdrawn from the trial treatment in the event of any of the following:Withdrawal of consent, orDue to serious adverse reactions (anaphylaxis, or suspected unexpected serious adverse reactions), which are clinically relevant and affect the patient’s safety, and discontinuation is considered necessary by the trial investigators (stopping rule). In case a stopping rule emerges, the sponsor in concert with the investigator/treating physician decides whether code breaking should be performed. Emergency code-breaking envelopes are stored at the Blood Bank and are opened at the initiative of the sponsor. It is documented in the case report form (CRF), if the code is broken.

All patients who withdraw from the trial for any reason and at any time should have an end-of-trial examination. Patients will be examined for any status changes that require further follow-up. All withdrawn patients will be followed up as the remaining patients in the trial. If consent is withdrawn, the person making the withdrawal will be asked for permission to follow up for 30 days after randomization.

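### The set labelled intention-to-treat is defined in two conflicting ways, neither of them all randomised patients, and the 24-hour replacement rule does not say that replaced patients stay in the analysis

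*Protocol article*

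**What the plan says.** The Statistical analysis section of the protocol article sets the efficacy population "according to the intention-to-treat principle comprising all patients who receive intervention (active or placebo), even if not completed". The sentence after it reads: "This includes all randomized patients fulfilling inclusion criteria and not meeting exclusion criteria". The per-protocol set is then a subset of this population, and its own definition again requires that the intervention was received.

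The sample-size text, printed under Missing data, adds: "Patients who drop out or are withdrawn for any reason before hour 24 will be replaced". The target is stated there as "We have chosen to include 40 patients, 20 evaluable patients in each randomization group in case of attrition, in the present trial".

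Other parts bear on the point:

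- **Patient withdrawal:** "All withdrawn patients will be followed up as the remaining patients in the trial". If consent is withdrawn, permission for 30-day follow-up is sought.
- **Interventions:** "The treating physician must have evaluated the patient’s eligibility and approved the patient’s enrolment in the trial prior to administration" of the study drug. The text does not say whether this comes before or after the envelope is opened.
- **Trial end points:** the primary end point is read 15 minutes after the intervention. Secondary end points include transfusion, 24-hour and 30-day mortality, time to intervention, and the percentage treated within an hour of arrival. Table 3 counts all time points from the infusion.

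**The concern.** An intention-to-treat comparison is protected because membership is fixed at randomisation. Here the first sentence makes membership depend on a later event, receipt of the infusion. The second makes it depend on eligibility, and one exclusion criterion (active treatment being withdrawn) can arise after allocation. The sentences select different patients, so two analysts following the same text could report different denominators.

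The replacement rule adds uncertainty. A patient who leaves at hour 20 may have a complete primary measurement and is still replaced. Nothing says whether that patient counts in the analysis, and the window overlaps 24-hour mortality.

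The comparison of transfusion and mortality is at stake, because patients never infused may be unusual in prognosis. So is what the trial can say about delivering the drug quickly.

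**Working it through.** **1. Who is in the set.** The two sentences side by side:

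| Randomised patient | First sentence (receipt) | Second sentence (eligibility) | All randomised |
|---|---|---|---|
| Eligible, infused | in | in | in |
| Eligible, not infused | out | in | in |
| Ineligible, infused | in | out | in |
| Ineligible, not infused | out | out | in |

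The sentences agree only on the first and last rows, and each omits patients whom an all-randomised set would hold. The per-protocol condition of having received the intervention would be redundant if the parent set were already defined by receipt, so the text does not settle which sentence governs.

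**2. The plan's own sample size.** Inputs from the article: SD 5.6 mm, lower end of the 6–8 mm effect, alpha 0.05, power 0.90. Sidedness is not stated; two-sided is assumed.

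n per arm = 2 × (1.960 + 1.282)² × 5.6² / 6² = 18.3, rounded up to 19.

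This matches the stated 19. The finding concerns the analysis set and not the arithmetic.

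**3. Loss of patients costs little power.** With n per arm, power = Φ(6 / (5.6 × √(2/n)) − 1.960). This gives 0.923 at n = 20, 0.910 at 19 and 0.895 at 18. The issue is selection more than precision, since one patient is 1/20 = 5% of an arm.

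**4. Sensitivity of mortality (illustration).** The Discussion expects 20% to die, without a time frame: 0.20 × 20 = 4 per arm. The article gives no rate of non-infusion, so assume that 0, 1 or 2 of those who die in one arm were never infused. The treated-only set then reports 4/20 = 20.0%, 3/19 = 15.8% or 2/18 = 11.1%. The all-randomised figure is 4/20 = 20.0% throughout.

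**5. Delivery end points (illustration).** Suppose 40 are randomised, u are never infused, and every infused patient is treated within the hour. A treated-only denominator gives 100% whatever u is. All randomised gives 39/40 = 97.5%, 38/40 = 95.0% and 37/40 = 92.5% for u = 1, 2, 3. Time to intervention behaves alike: in a treated-only set every patient has the event.

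**6. Cost of analysing everyone.** If k of 20 active patients are not infused, are counted, and gain nothing, the mean difference is 6 × (20 − k)/20.

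| k | Difference (mm) | Power, SD 5.6 | Power, added spread in active arm |
|---|---|---|---|
| 0 | 6.0 | 0.923 | 0.923 |
| 1 | 5.7 | 0.896 | 0.888 |
| 2 | 5.4 | 0.862 | 0.845 |
| 3 | 5.1 | 0.821 | 0.794 |

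The last column uses an active-arm variance of 5.6² + 6² × p(1 − p), with p = k/20.

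**7. Link to the missing-data rule.** The plan imputes when fewer than 95% of observations are complete and uses complete cases when more than 95% are. If the uninfused patients of step 5 lack a post-infusion value and are kept in the set, completeness is 97.5%, 95.0% or 92.5% for one, two or three of them. If they are dropped, it is 100%. So the choice of set can decide which method is applied.

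**The case against.** The strongest reply is that this is a wording fault with little consequence. Allocation is concealed in sealed, opaque envelopes. The nurse who opens one is not involved in treating that patient, and opaque syringes and coloured infusion sets hide the content from the treatment team. A decision not to infuse should therefore not depend on arm, and bias in a 15-minute laboratory measure should be small. That stands, provided blinding works and nearly all randomised patients are infused. It does not repair the contradiction.

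Several stronger readings are tempting, and the documents do not support them:

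- **Eligibility is re-judged after allocation.** A reader might infer this because approval is required only before the drug is given. The article describes no later eligibility review, and its silence on the envelope is not evidence of one.
- **Replacement removes patients.** It adds a patient. An infused patient who leaves at hour 20 still meets the receipt definition and is followed up. The gap is that retention is not stated.
- **Early deaths are replaced.** The phrase about any reason could be stretched to cover death, but the withdrawal section speaks of consent and adverse reactions, and mortality is an end point recorded at 24 hours.
- **Replacement is made within arm, by looking up the allocation.** The target of 20 evaluable per group might suggest it. The article does not say so, and the list is withheld from the investigator until completion. It describes a list of "were arranged in two groups of 20 patients in a single column in a systematic order" and does not say where a replacement's allocation comes from.
- **Delivery end points cannot show non-delivery.** This follows only if the receipt-defined set is used for them. That set is named for efficacy analyses, and the Cox model's mention of competing risks suggests that some patients might never be infused.

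A practical objection also stands: a patient never infused has no 15-minute post-infusion value, so any all-randomised set must say how that patient is handled.

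**Conclusion.** The point holds. The efficacy set is mislabelled and defined inconsistently, and the fate of replaced patients is left open although the primary end point is complete long before the 24-hour limit.

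For the primary end point the likely effect is small, given working blinding and near-complete infusion. The exposure is greater for transfusion and mortality. In an arm of 20 with four deaths, one uninfused death moves the reported figure from 20.0% to 15.8%; this rests on an assumed count and on a mortality figure without a time frame. For the delivery end points, a treated-only denominator would hide non-delivery entirely.

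It would go too far to say that randomisation no longer protects the comparison. The article shows no route by which exclusion is driven by arm. It only leaves the set open to events after randomisation.

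**What to change.** - Define the intention-to-treat set as all randomised patients whose data may be used, in their allocated arm, whether or not infused and whether or not later found ineligible. Replace both present sentences with this one.
- Use it for mortality, transfusion and the delivery end points. For patients never infused, count time from randomisation or arrival, and state which.
- For TEG end points, handle the absent post-infusion value of an uninfused patient under the plan's missing-data rule. Report the treated-only set, named modified intention-to-treat, as a sensitivity analysis.
- State that replaced patients with usable data stay in the analysis, that death is an outcome and not a drop-out, and that a replacement takes the next numbered envelope without reference to arm.

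**Cost.** Mostly wording. The article reports recruitment as ongoing, so it could be settled before the code is broken. The total analysed may exceed 40. If uninfused active patients are counted with no gain, power at 6 mm (SD 5.6, 20 per arm) falls from about 0.92 to 0.90 with one and 0.86 with two. If their TEG value is instead treated as missing and complete cases are used, the cost is the lost observation, as in step 3 of the working.

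### The last fallback for the primary test drops the baseline adjustment and, if reached at the 6 mm planning effect, can fall short of 90% power

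*Protocol article*

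**What the plan says.** The Statistical analysis section sets the primary analysis: "The change in TEG® FF MA from baseline to the 15-min measurement will be analysed with ANCOVA". It gives the reason for the covariate: "The analysis will be adjusted for baseline TEG® FF MA to increase statistical power". Residuals are judged on QQ-plots, and two fallbacks follow in order. First, "if a satisfactory fit is not obtained, we will first attempt to conduct the analysis using log-transforms". Second, "If the fit is still not adequate, we will employ the Mann-Whitney test to the change values".

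The same chain is set for secondary end points 1 to 4 of Table 2, ending in: "we will employ the Mann-Whitney test to the measured changes from baseline to each of the measurement times".

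The sample size paragraph, printed under Missing data, rests on "TEG® FF MA mean 13.6 mm (SD ± 5.6) on arrival in trauma patients not surviving for 30 days" and on a dose that "will result in an approximate increase of 6–8 mm in TEG FF MA". It arrives at 19 per group for 90% power at alpha 0.05, with 20 per group planned. It then says: "The actual statistical power will be a bit higher as the primary end point is a change value". The sentence goes on to give the baseline adjustment as a second reason. The next sentence concedes that the intra-person correlation is not reliably known.

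**The concern.** Three things do not fit together.

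- **The covariate is lost.** Baseline is in the model to gain power, yet the final fallback is a two-sample rank test on raw changes with no covariate. Subtracting baseline is not the same as adjusting for it. When the two measurements are weakly correlated, subtraction adds noise.
- **The log step is open.** The text does not say what is logged. If it is the change, one zero or negative value stops the step and the plan moves on to Mann-Whitney.
- **The power sentence gives two reasons, and only one is sound.** The planning SD belongs to a single arrival value. A change has a larger SD than that whenever the correlation is below 0.5.

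At stake is the power of the primary comparison in a 40-patient trial, in the case where the residual plots look poor.

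**Working it through.** **Inputs.** From the article: SD 5.6 mm (one arrival value), effect 6 to 8 mm, alpha 0.05, power 0.90, 19 per group required, 20 planned. Not in the article, so assumed: correlation rho between baseline and 15-min FF MA, varied from 0 to 0.8; equal SD at both times; zero mean placebo change; additive treatment effect; two-sided test.

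**Reproducing the plan's n.** n per group = 2(1.960 + 1.282)² × SD² / d².
- d = 6: 2 × 10.51 × 31.36 / 36 = 18.3, so 19. This matches.
- d = 7 gives 14 and d = 8 gives 11.

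So 19 rests on the 6 mm end of the range and on the SD of a single value. Exact t-test power at 6 mm is 0.895 with 19 per group and 0.910 with 20.

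**SD of what each method analyses.**
- Change: 5.6 × √(2(1 − rho)).
- ANCOVA residual: 5.6 × √(1 − rho²).
- Variance ratio, change to ANCOVA: 2(1 − rho)/(1 − rho²) = 2/(1 + rho).

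| rho | SD of change (mm) | ANCOVA SD (mm) | variance ratio |
|---|---|---|---|
| 0.3 | 6.63 | 5.34 | 1.54 |
| 0.5 | 5.60 | 4.85 | 1.33 |
| 0.7 | 4.34 | 4.00 | 1.18 |

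The change has the planning SD of 5.6 only at rho = 0.5. At rho = 0 its SD is 7.92. The ANCOVA SD never exceeds 5.6.

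**Power by simulation, normal data, 6 mm, 20 per arm** (10,000 runs per cell):

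| rho | Mann-Whitney on change | ANCOVA |
|---|---|---|
| 0 | 0.61 | 0.90 |
| 0.2 | 0.71 | 0.91 |
| 0.3 | 0.77 | 0.93 |
| 0.4 | 0.83 | 0.94 |
| 0.5 | 0.90 | 0.97 |
| 0.6 | 0.95 | 0.98 |
| 0.7 | 0.99 | 1.00 |

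Repeat runs with other seeds agreed to within about 0.02. Rank ANCOVA gave 0.91, 0.91, 0.93 and 0.96 at rho 0.2, 0.3, 0.4 and 0.5; a repeat run gave 0.90 at rho 0.2.

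**Where Mann-Whitney reaches 90% power.**
- 6 mm, normal data: rho about 0.50 with 20 per arm, 0.54 with 19.
- 7 mm: about 0.34. 8 mm: about 0.14 (20 per arm).
- 6 mm, heavy-tailed or skewed data: roughly 0.35 to 0.4.

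**Non-normal data, 6 mm, 20 per arm.** These are the conditions that would trigger the fallback. At rho 0.2, Mann-Whitney power was 0.78 to 0.85 depending on the shape, and rank ANCOVA was 0.95 or more. With t-distributed data on 4 df at rho 0.2, 0.3, 0.4 and 0.5, Mann-Whitney gave 0.81, 0.86, 0.90 and 0.94, ANCOVA 0.92, 0.92, 0.93 and 0.95, and rank ANCOVA 0.96, 0.96, 0.97 and 0.98. Type I error at rho 0.3 was 0.04 to 0.06 for all three tests, so the fallback bought no validity in these settings.

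**The log step.** If the mean placebo change is zero, half of the placebo changes are zero or negative. In the active arm at 6 mm the share is Φ(−6/SD of change): 22% at rho 0, 14% at 0.5 and 5% at 0.8. The zero is an assumption. At rho 0.5, a placebo mean of +2 mm gives Φ(−2/5.6) = 36%, and −2 mm gives 64%. Over that range, the log of a raw change is undefined for many patients. A shift common to both arms cancels in the comparison, so the power figures do not depend on it.

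**The case against.** The strongest reply is that the loss belongs to a branch, not to the trial. Mann-Whitney is reached only after two failed fits. With a Shapiro-Wilk test at 0.05 standing in for a poor QQ-plot and the log step skipped, power of the whole procedure at 6 mm was at least 0.91 for normal data (fallback triggered about 5% of the time) and for heavy-tailed data (about 31%). It fell to 0.86–0.90 only for skewed data at rho 0.2 to 0.3. This stands. A reader might infer that the trial lacks its stated power, and the documents do not support that.

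A reader might also infer that the log step cannot be run. The article does not say that the change is logged. Logging the 15-min and baseline values fits the wording, is feasible for a positive amplitude, and agrees with Table 2, which lists the primary end point as the 15-min value. What remains is an unnamed variable and one natural reading that fails.

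The 0.5 threshold is not general: it needs 6 mm and normal data. With heavy tails and higher correlation Mann-Whitney catches up (0.978 against 0.971 for ANCOVA at rho 0.6, 4 df). The power sentence does cite the baseline adjustment, and for ANCOVA its conclusion is right. The sequence is pre-specified and run by a statistician blinded to allocation, which limits biased choice of test. That blinding does not restore the covariate.

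**Conclusion.** The point holds, at moderate severity. The planned ANCOVA keeps about 90% power or more at 6 mm with 20 per arm at every correlation examined. The last fallback does not: if reached, its power is about 0.71 to 0.83 for correlations of 0.2 to 0.4 with normal data, and it stays under 90% below a correlation of roughly 0.35 to 0.4 with heavy-tailed or skewed data. These figures assume equal SDs of 5.6 mm and an additive effect; at 7 to 8 mm the shortfall is confined to lower correlations. Rank ANCOVA avoids it at almost no cost.

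Being a change value does not by itself raise power when the correlation is unknown; only the baseline adjustment supports that statement. The log step needs its variable named.

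**What to change.** - Keep the baseline-adjusted ANCOVA in mm as the primary analysis.
- State that any log analysis is of log 15-min FF MA adjusted for log baseline FF MA.
- Replace Mann-Whitney on changes with rank ANCOVA, or with a permutation test of the ANCOVA statistic, so that baseline stays in the model. Do the same for the TEG secondary end points.
- Restrict the statement about higher power to the baseline-adjusted ANCOVA, and delete the change value as a reason.

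The cost is a few lines of wording and code, with no effect on trial conduct or sample size. A rank ANCOVA gives no estimate in mm, so the ANCOVA estimate in mm with its confidence interval should be reported beside it.
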